### Patient and public involvement

2.9

There will be no patient or public involvement in the conduct, reporting, or dissemination of this research.

### Participant timeline

2.10

The post-enrollment timeline starts when the patient enters the operating room and ends when the patient leaves the PACU. All relevant variables will be recorded by individuals who are unaware of the grouping. The follow-up staff will evaluate the patient’s postoperative nausea and vomiting 48 h after the surgery to assess the relevant situation (Table 1).

**Table 1 tab1:** Study flow chart.

**Timepoint**	**-D1**	**-D1**	**D01**	**D02**	**PACU**	**2 h**	**6 h**	**12 h**	**24 h**	**48 h**	**D03**
Enrollment											
Patient screening	√										
Informed consent	√										
Allocation		√									
Random assignment		√									
Intervention:											
[EA group]			√								
[CA group]			√								
[EB group]			√								
[CB group]			√								
Assessments:											
Eligibility criteria		√									
Baseline data		√									
[Vital signs]		√									
[ESPB and assessment]			√								
[NLR]		√							√		
[PONV score]					√	√	√	√	√	√	
[Antiemetic requirements]					√	√	√		√	√	
[VAS score]					√	√	√	√	√	√	
[Consumption of propofol or remifentanil or analgesics]				√	√	√	√	√	√	√	
[The first pressanalgesia pump]					√	√	√	√	√	√	
[Pain satisfaction scores]					√	√	√		√	√	
[Extubation time]					√						
[PACU stay time]					√						
[NETs]									√		
[Postoperative discharge time]											√
Occurrence of adverse reactions:						√	√	√	√	√	
[Dizziness]					√	√	√	√	√	√	
[Urinary retention]					√	√	√	√	√	√	
[Other adverse reactions]					√	√	√	√	√	√	

-D1, The day before surgery; D01, Day of surgery, before the start of the operation; D02, During surgery; D03, Postoperative discharge time; ESPB, erector spinae plane block; NLR, neutrophil to lymphocyte ratio; PONV, postoperative nausea and vomiting; NETs, neutrophils form neutrophil extracellular traps.

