### Intervention

2.6

For patients undergoing posterior lumbar spine surgery under general anesthesia, a researcher will assess whether the patient meets this study’s inclusion and exclusion criteria 1 day before the surgery. The participants who meet the inclusion criteria must sign an informed consent form after being fully informed of the study procedures, potential benefits, and risks. Preoperatively, the NLR will be calculated by dividing the neutrophil count by the lymphocyte count. The pre-calculated NLR threshold of 2 will be accepted. Patients with a preoperative NLR < 2 will be included in Group A (*n* = 110); those with a preoperative NLR > 2 will be included in Group B (*n* = 110). Using a random number table, Group A will be divided into ESPB (EA group, *n* = 55) and control groups (CA group, *n* = 55); Group B will be divided into ESPB (EB group, *n* = 55) and control groups (CB group, *n* = 55). The researcher will allocate the drugs using an envelope method to conceal the randomization sequence; a specially trained anesthesia nurse will deliver the implementation plan to the corresponding operating room before surgery.

ESPB Group (EA group + EB group): Routine anesthesia induction, followed by ultrasound-guided bilateral ESPB with 0.5% ropivacaine (20 mL) after anesthesia induction.Control Group (CA group + CB group): Routine anesthesia induction, followed by ultrasound-guided bilateral ESPB injection with 0.9% saline (20 mL) after anesthesia induction.

Upon entering the operating room, standard intravenous access will be established; noninvasive blood pressure, electrocardiogram, and oxygen saturation (SpO_2_) will be monitored. Considering that most patients undergoing this surgery are older and positioned prone, radial artery catheterization will be performed using the FloTrac sensor to enable invasive blood pressure monitoring and ensure patient safety. All patients will receive total intravenous anesthesia.

With the patient in the supine position, a face mask will be used for oxygenation and denitrogenation for 3 min before anesthesia induction. Anesthesia induction will include midazolam (0.02 mg/kg), sufentanil (0.2–0.3 μg/kg), propofol (1.5–2 mg/kg), and atracurium (0.6 mg/kg). After the disappearance of the eyelash reflex and jaw relaxation, tracheal intubation will be performed using a visual laryngoscope, and the endotracheal tube will be secured. Mechanical ventilation will be initiated by adjusting respiratory parameters.

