Throughout the study, data will be gathered and managed securely and privately. Data will be collected automatically via the anesthetic information system and vital sign monitoring system. A nursing anesthetist will also collect some data manually. Participants will be identified throughout the study using code numbers rather than names unless otherwise specified. All relevant records and files will be archived for 5 years. During the study, the data will be accessible only to researchers who have signed confidential disclosure agreements and institutional or government auditors. Data without patient identification will be accessible to the general public after the study concludes.

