#### Secondary outcome measure

2.8.2

The secondary outcomes include the following variables: (1) VAS scores during rest and movement for patients at 2, 6, 12, 24, and 48 h postoperatively; (2) consumption of propofol, remifentanil, and other drugs during surgery, as well as the total consumption of analgesics in the first and second 24-h periods postoperatively; (3) the time of the first press on the patient-controlled analgesia pump, pain satisfaction scores at 24 and 48 h, postoperative recovery time, extubation time, PACU stay time, and postoperative discharge time; (4) the occurrence of opioid-related side effects such as dizziness and urinary retention; (5) the concentration of NETs in serum on the first postoperative day.

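### Table 1 schedules adverse-reaction recording only from the PACU or 2 h, so a by-arm comparison would omit the period right after the study injection

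*Protocol article*

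**What the plan says.** **Timing of the injection.** Section 2.6 has the randomised treatment given once the patient is asleep: "followed by ultrasound-guided bilateral ESPB with 0.5% ropivacaine (20 mL) after anesthesia induction" in the block arms, and the same volume of saline in the control arms. Table 1 places all four intervention rows in column D01. Its footnote defines the columns as "D01, Day of surgery, before the start of the operation; D02, During surgery".

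**Timing of adverse-reaction recording.** Table 1 carries a heading row, "Occurrence of adverse reactions", and beneath it rows for dizziness, urinary retention and "Other adverse reactions". The heading row is ticked at five times and each sub-row at six. All of these times fall after the operation.

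**Span of the schedule.** The text above Table 1 says: "The post-enrollment timeline starts when the patient enters the operating room and ends when the patient leaves the PACU".

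**Other relevant entries.** Table 1 ticks "ESPB and assessment" at D01 and does not say what is assessed. The safety-type outcome in section 2.8.2 is the item "4) the occurrence of opioid-related side effects such as dizziness and urinary retention". Section 2.7 states: "Data will be collected automatically via the anesthetic information system and vital sign monitoring system".

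**The concern.** The two arms differ in one thing, the solution injected at D01. A reaction to that injection, or to the needle, would be expected soonest in the minutes that follow, with the patient under general anaesthesia and unable to report symptoms then or recall them later. A site that follows Table 1 to the letter would begin filling in adverse-reaction fields only when the patient reaches the PACU, or at 2 h if it follows the heading row.

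What is at stake is the content of the adverse-reaction table in the trial report. The general row looks like a count of all other reactions by arm, but it would cover only the postoperative part of each patient's exposure. A reader of that table would not know that the interval from injection to PACU arrival had been left out. There is also a practical problem: two start times are printed for what should be one schedule, so PACU events may be handled inconsistently.

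**Working it through.** No formula applies and the plan gives no figure to reproduce. The check is a row-by-row reading of Table 1 against the text.

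**Step 1: are the columns aligned?** The column order is -D1, -D1, D01, D02, PACU, 2 h, 6 h, 12 h, 24 h, 48 h, D03. Rows with a known time land where they should. NLR falls at -D1 and 24 h and NETs at 24 h, consistent with the first postoperative day in section 2.8. Extubation and PACU stay fall in the PACU column, and discharge time falls at D03. The extracted table can therefore be read by position.

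**Step 2: tick positions for adverse reactions.**

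| Row | D01 | D02 | PACU | 2 h | 6 h | 12 h | 24 h | 48 h | Ticks |
|---|---|---|---|---|---|---|---|---|---|
| Heading row | – | – | – | yes | yes | yes | yes | yes | 5 |
| Dizziness | – | – | yes | yes | yes | yes | yes | yes | 6 |
| Urinary retention | – | – | yes | yes | yes | yes | yes | yes | 6 |
| Other adverse reactions | – | – | yes | yes | yes | yes | yes | yes | 6 |

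None of the four rows is ticked at D01 or D02.

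**Step 3: set against the injection.** The injection is at D01 and the operation at D02. Both precede the first tick in every row, so the unscheduled interval runs from needle insertion to PACU arrival for every patient: 55 + 55 = 110 in the ropivacaine arms and 55 + 55 = 110 in the saline arms, 220 in total. The article gives no operating time, and the point does not depend on one.

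**Step 4: internal consistency.** The heading row starts at 2 h and its own sub-rows start at the PACU. The section 2.10 text starts the timeline at operating-room entry, earlier than either. That sentence also ends the timeline at PACU departure while the table runs to 48 h and discharge, so it is loose at both ends and needs aligning anyway.

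**Step 5: could the schedule have covered surgery?** Yes. Column D02 exists and is used for drug consumption. Column D01 exists and is used for the block and its assessment.

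**Step 6: other routes by which an acute event might be captured.**
- The D01 block assessment: its content is undefined, and it is listed under assessments, not adverse reactions.
- Automatic capture (section 2.7): it supplies source data, but the article does not turn these into an adverse-reaction variable or a by-arm comparison.
- Other drugs used during surgery (section 2.8.2, item 2): this could cover drugs given when blood pressure or heart rate moves beyond the 20% limit in section 2.6. The matching row of Table 1, however, names only propofol, remifentanil and analgesics.
- The CRF note on emergency unblinding (section 2.12): it covers only events serious enough to break the blind.

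Each route is partial. None gives a scheduled count of acute events by arm.

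**The case against.** The strongest reply has four parts.

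1. **The events are not lost.** Patients have ECG, oxygen saturation and invasive arterial pressure monitoring, the systems store data automatically, and the routes in step 6 exist. This stands. A reader might infer from Table 1 that acute reactions would never be recorded; the documents do not support that. They support only the narrower statement that such events are not scheduled to be counted as adverse reactions.

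2. **No safety claim is planned.** A reader might infer that the trial would conclude the block is safe from the wrong window. No objective, outcome or stated conclusion concerns block safety. The remark in the Introduction about an absence of apparent adverse reactions is cited background on earlier use of the technique. This stands too. One could calculate that zero events in 110 patients gives a one-sided 95% upper bound of 1 − 0.05^(1/110) = 2.7%, but that serves an inference the trial does not propose. Nor is a bias towards no difference shown, since that would require acute events that occurred, differed by arm and went uncounted.

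3. **The window suits the named outcome.** Dizziness cannot be assessed under anaesthesia, and opioid side effects are postoperative. This stands for dizziness and urinary retention. It does not explain the general row, which is not limited to opioid effects. Section 2.12 itself foresees that the study drug may affect safety. The vital-signs tick at -D1 sits just below baseline data and does not mean that monitoring is absent later.

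4. **This is a condensed article.** Adverse-event definitions and CRF detail may sit in the full protocol, and their absence here is no fault. But the article does print a schedule, and that schedule has a stated start that conflicts with itself. The heading-row ticks may be a layout slip, since no other heading row in Table 1 carries any. That makes the conflict easy to correct but does not supply the missing D01 and D02 entries.

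**Conclusion.** The point holds as a minor one. As printed, Table 1 starts adverse-reaction recording at the PACU (sub-rows) or at 2 h (heading row), after both the injection and the operation. This applies to all 220 patients and to all four adverse-reaction rows. It matters for the general row only; a PACU start is reasonable for dizziness and urinary retention. The consequence is conditional: if adverse reactions are compared by arm from these fields, the comparison omits the interval from injection to PACU arrival, although events that persist into or first appear in the PACU would be picked up.

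This rests on two assumptions: that Table 1 reflects the CRF, and that no unshown document defines the D01 assessment as adverse-event recording. The primary outcomes and their analysis are not touched.

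**What to change.** - In Table 1, tick the general adverse-reactions row at D01 and D02. Leave dizziness and urinary retention starting at the PACU.
- Make the heading row agree with its sub-rows, or remove its ticks as for the other heading rows. Align the section 2.10 sentence on the timeline's start and end with the table.
- State that the D01 block assessment records events related to the study injection, from needle insertion.
- Report these events by arm. Alongside them, tabulate by arm the haemodynamic deviations beyond the 20% threshold already in section 2.6, taken from the anaesthetic information system.
- The Abstract says recruitment is under way. For patients already treated, extract the same items from the stored records before unblinding, by someone unaware of allocation.

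The cost is two table ticks, a clarifying line and a CRF field. The source data are already collected, and nothing in treatment or monitoring changes. The only downside is a slightly longer adverse-event listing.

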### Sample size calculation

2.11

To calculate the sample size for the primary research objective, use the “Tests for Two Ordered Categorical Variables” module in PASS software. Set the test power to 1 − β = 0.8 and significance level *α* = 0.05; use a 1:1 ratio between the NLR < 2 and NLR ≥ 2 groups. For the NLR < 2 group, the composition ratios of the PONV states considered as no, nausea, retching, and vomiting are 0.575, 0.050, 0.001, and 0.375, respectively. For the NLR ≥ 2 group, the composition ratios for PONV no, nausea, retching, and vomiting are 0.250, 0.100, 0.050, and 0.600, respectively. The calculated sample size is 94 cases, considering a 10% dropout rate. The final sample size is 106, with 53 patients in each group.

Use the “Tests for Two Proportions” module in PASS software to calculate the sample size for one of the secondary objectives: determining whether preoperative NLR can serve as a biomarker for PONV. Set the test power to 1 − β = 0.8 and significance level to *α* = 0.05; use a 1:1 ratio between the control and thoracic paravertebral nerve block groups. Nausea and vomiting rates are 8.3 and 33.3%, respectively. The calculated sample size is 82, considering a 10% dropout rate. The final sample size is 92, with 46 patients in each group.

The baseline NLR levels are first divided into two strata, and randomization is performed within each stratum. The sample size of each group in this study is 55.

### Randomization and blinding

2.12

Patients are grouped using block randomization; drug blinding is conducted by specialized personnel who are not directly involved in the clinical trial. Block randomization will be performed using random number tables generated by the SAS statistical software.

This trial is designed to be double-blinded; both the participants and follow-up personnel will be unaware of the group assignments. The overall randomization table is maintained by the personnel responsible for the statistics. The researchers prepare the drugs using an overall randomization table. Postoperative follow-up is conducted by anesthesia nurses who have received specialized training. Unblinding is conducted according to the normal procedures if no emergencies occur during the study. After the trial concludes, the Clinical Report Form (CRF) will be checked. Following signatures, unblinding will be performed to determine the group assignments of the study participants for statistical analysis and evaluation of efficacy differences between the experimental and control groups. Emergency unblinding is allowed only when the study drug affects the treatment or safety of the study participants. The principal investigator will be notified, and emergency unblinding will be performed based on the drug information provided in the emergency letter. This information will be noted in the CRF.

### Statistical analysis

2.13

All data will be statistically analyzed using SPSS software (version 25.0). Continuous variables such as VAS scores will be represented by the mean ± standard deviation if they follow a normal distribution. An independent sample t-test will be employed to compare intergroup differences. If the data do not conform to a normal distribution, the Wilcoxon rank-sum test will be used to compare groups.

For categorical variables, such as sex, the chi-squared or Fisher’s exact test will be used to assess intergroup differences. For ordinal data, such as the degree of vomiting, the Wilcoxon rank-sum test will be used for between-group comparisons.
